#### Secondary Efficacy and Implementation Outcomes

If there is a provider-level effect, we will use mixed-effect GLM to look at the association of STIckER on the continuous outcomes, such as implementation scales, and linear or logistic regression if there is no provider effect. If needed, we will also conduct sensitivity analyses to explore the effect of spillover, misclassification, missing data, or any other deviation from the study procedures that would affect efficacy or implementation outcomes.

#### Exploratory and Subanalyses

Additional exploratory analyses will examine differences in the primary and secondary outcomes among adolescent and young adult patients by age (older vs younger), gender, sexual identity, and other covariates of interest. Analyses of providers will include exploring differences by gender, years of professional experience, and other covariates where possible.

### Power Analysis

This pilot trial will enroll 44 providers and 140 adolescent and young adult patients over 6 months based on feasibility. Using a simple, parallel randomized design and accounting for providers evaluating more than 1 patient, we estimate the minimum detectable effect size (MDE) of 0.348. MDE is based on the following assumptions: α=.05, a 2-tailed test, with 80% power, and ICC of 0.01, 50% of variance in adolescents and young adults, and 50% of variance in providers explained, and all other covariates of interest (eg, age and gender) were balanced by randomization of STIckER to providers and their adolescent and young adult patients. With our sample size of 140 participants, we have the power to detect a minimum of 35% higher likelihood of being tested for STIs in the intervention arm compared to usual care.

The ICC of 0.01 and the assumption that 50% of the variance would be attributable to provider- versus patient-level factors were based on conservative estimates. These assumptions are intended to ensure sufficient power while accounting for possible provider clustering.

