#### Randomization and Allocation

To avoid contamination, 50 HCPs were randomized 1:1 to the intervention (STIckER) or control arm. The allocation sequence was computer-generated by the study epidemiologist using a simple randomization method with stratification by location (adult vs pediatric ED). The randomization sequence was implemented by a study coordinator using a centralized allocation system. The assignment was not concealed from investigators. Randomization health care provider participant (HCP-P) in the intervention arm received 1:1 training with a research assistant on the STIckER app. If a participating provider left the ED before the end of the study period, a new provider randomized to the same study arm was invited to participate.

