#### Preliminary Efficacy

An intent-to-treat analysis of all enrolled patients will be conducted according to random assignment of the intervention to estimate the effect of STIckER on STI testing. We will conduct a mixed-effects generalized linear model (GLM) with the logit link function to look at the effect of STIckER on STI testing, if there is a clustering effect by provider, or logistic regression if there is no provider effect. To determine whether there is a provider effect, we will assess the intraclass correlation coefficient (ICC) for the primary outcome using a null (empty) mixed-effects model with provider as a random effect. If the ICC is greater than 0.01, we will proceed with mixed-effects modeling; otherwise, we will use standard logistic regression. For other dichotomous outcomes, we will use the same analytic approach (GLM) with the logit link function if there is a provider effect or logistic regression if there is no provider effect.

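### The MDE of 0.348 at 80% power needs half of the patient-level variance to be explained, yet the article names no covariate in the primary model and calls this input conservative

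*Protocol article*

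**What the plan says.** The Power Analysis section fixes the size on practical grounds: "This pilot trial will enroll 44 providers and 140 adolescent and young adult patients over 6 months based on feasibility". From that size it derives a detectable effect: "we estimate the minimum detectable effect size (MDE) of 0.348". The listed assumptions are "α=.05, a 2-tailed test, with 80% power, and ICC of 0.01", followed by "50% of variance in adolescents and young adults, and 50% of variance in providers explained". Other covariates, with age and gender as examples, are taken to be balanced by the randomization.

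The section's second paragraph describes the 50% input again, differently: "the assumption that 50% of the variance would be attributable to provider- versus patient-level factors were based on conservative estimates" (the ICC of 0.01 shares this verdict).

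For the primary analysis, the Preliminary Efficacy section says: "We will conduct a mixed-effects generalized linear model (GLM) with the logit link function to look at the effect of STIckER on STI testing", or ordinary logistic regression if the estimated ICC does not exceed 0.01. It lists no covariates. Age, gender and sexual identity appear under Exploratory and Subanalyses.

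**The concern.** An R-squared input lowers the MDE only if the analysis contains covariates that explain that share of the outcome variance. Balance between arms does not do this: it removes confounding and leaves the residual variance where it was. The article claims the gain from a 50% R-squared without naming any variable that would deliver it.

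The second paragraph makes matters worse in two ways. It turns variance explained at each level into variance divided between levels, which is a different quantity. It also tells the reader that the inputs err on the safe side, when both push the MDE down.

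What is at stake is interpretation. Enrolment is complete and analysis is under way, so a null or imprecise result would be read against a claimed 80% power at 0.348. The same inputs could also be carried into the sample size of the multisite trial that this pilot is meant to inform.

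**Working it through.** **Inputs.** From the Power Analysis section: J = 44 providers, N = 140 patients ("With our sample size of 140 participants"), two-sided alpha 0.05, power 80%, ICC 0.01, and R-squared 0.5 at patient and at provider level. From Randomization and Allocation: 1:1 assignment by provider, so P(1−P) = 0.25.

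**Formula** (standard two-level cluster-randomized MDE, in SD units):

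MDE = M × √[ ICC(1−R²_provider)/(0.25·J) + (1−ICC)(1−R²_patient)/(0.25·N) ]

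Here 0.25·J = 11 and 0.25·N = 35. M = t(0.975) + t(0.80) on J−2 = 42 df = 2.868.

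**Step 1: reproduce the plan's figure.**
√[0.01×0.5/11 + 0.99×0.5/35] = √0.01460 = 0.1208. MDE = 2.868 × 0.1208 = 0.347, and power at 0.348 is 80.3%. The stated 0.348 is therefore a standardised effect from this type of formula. Small differences come from rounding choices: 132 patients (3 per provider) with normal quantiles gives 0.3483.

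**Step 2: which R-squared matters?**

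| R² patient | R² provider | MDE |
|---|---|---|
| 0.5 | 0.5 | 0.347 |
| 0.5 | 0 | 0.352 |
| 0 | 0.5 | 0.486 |
| 0 | 0 | 0.490 |

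The patient-level input does nearly all the work.

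**Step 3: no covariates.**
√[0.01/11 + 0.99/35] = √0.02920 = 0.1709. MDE = 2.868 × 0.1709 = 0.490, which is 41% above 0.347. Equivalently, the 50% input cuts the MDE by 29%. Power at 0.348, from the noncentral t with 42 df and noncentrality 0.348/0.1709, is 51.2%. With normal quantiles, other df, 132 or 139 patients, or 50 providers (the number in "50 HCPs were randomized 1:1 to the intervention (STIckER) or control arm"), it stays between 49% and 53%.

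**Step 4: partial adjustment** (same R² at both levels, ICC 0.01).

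| R² | Power at 0.348 | MDE at 80% power |
|---|---|---|
| 0 | 51% | 0.490 |
| 0.1 | 55% | 0.465 |
| 0.2 | 60% | 0.438 |
| 0.3 | 66% | 0.410 |
| 0.4 | 73% | 0.380 |
| 0.5 | 80% | 0.347 |

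**Step 5: direction of the ICC** (R² = 0). ICC 0.01, 0.05 and 0.10 give MDEs of 0.490, 0.511 and 0.535. A smaller ICC is the favourable choice, and 0.01 is also the plan's own threshold at or below which clustering would be ignored. With about 140/44 = 3.2 patients per provider, the effect is modest: 4% at ICC 0.05 and 9% at ICC 0.10.

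**Step 6: percentage points.** The article gives no control testing rate, so rates of 20% to 50% are assumed here. By the arcsine conversion, p₂ = sin²(arcsin√p₁ + d/2), d = 0.49 corresponds to 20%→42%, 30%→54%, 40%→64% and 50%→74%, or about 22 to 24 points. For d = 0.348 the difference is about 15 to 17 points.

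**Cross-check on the binary scale.** A two-proportion comparison used 70 per arm, deflated by the design effect 1 + (3.18−1)×0.01 = 1.022. The difference was 0.348 × √[p(1−p)], with p the control rate. Unadjusted power is 45% to 54% for control rates of 20% to 50%, in line with Step 3.

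**The case against.** The strongest reply is that the article never calls the primary model unadjusted. It gives the model family and the effect of interest and is silent on covariates, and a covariate list may sit in an analysis plan that is not shown. Listing explained variance as an input even suggests that some adjustment was intended. This stands. A reader might infer that the trial simply has 51% power, but the documents do not support that: 51% is conditional on R-squared 0, and prognostic covariates would place power between 51% and 80%.

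A reader might also take the second description of the 50% input as a rival assumption of an ICC near 0.5, for which the unadjusted MDE would be 0.70. That reads too much into it. The same sentence repeats the ICC of 0.01, so this is a garbled restatement of the R-squared inputs. Only the wording conflicts.

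Two further points have force. The formula is for a continuous outcome, and adjustment in a logit model does not act as a simple reduction of residual variance, so every figure here is approximate. The comparison is nevertheless like for like, because 0.348 comes from the same formula. Second, this is a pilot sized on feasibility, so neither the sample size nor the analysis turns on the MDE. That lowers the severity, but the Primary Outcome section does say the trial was powered to give an effect size estimate, and an 80% figure is stated. Neither reply justifies the word conservative.

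**Conclusion.** The point holds as a correction to the stated power; it is not a flaw that invalidates the trial. The 0.348 at 80% power depends on a patient-level R-squared of 0.5 for which the article names no covariate. Taken as described, without covariates and at ICC 0.01, the same formula gives an MDE of about 0.49 SD and about 51% power at 0.348. The loss is smaller to the extent that prognostic covariates are in fact used. The provider-level R-squared hardly matters, and the ICC matters only moderately.

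Two faults need no assumption about an unseen plan: the second paragraph misdescribes the 50% input in words that, taken literally, conflict with ICC 0.01, and it labels as conservative two inputs that both make the MDE smaller.

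**What to change.** Either restate the MDE for the model as described, or supply what the 50% requires.

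- **Restate:** about 0.49 SD at ICC 0.01 and R-squared 0, with rows for ICC 0.05 (0.51) and ICC 0.10 (0.54). Give the equivalent in percentage points, about 22 to 24 for control rates of 20% to 50%, and label those rates as assumed. Note that the formula is approximate for a binary outcome.
- **Or justify:** name the baseline covariates in the primary model, give grounds for their R-squared, and recompute the MDE with it.
- **In both cases:** delete the word conservative, and replace the attribution wording with variance explained by covariates at each level.

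The cost is a less favourable stated figure. No additional patients are needed, and the first option leaves the primary analysis as described.

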### Outcomes

#### Primary Outcome

The primary outcome of preliminary efficacy is the difference in the proportion of sexually active adolescents and young adults tested for Neisseria gonorrhoeae or chlamydia trachomatis between the 2 arms based on the EMR review. We selected preliminary efficacy as the primary outcome because the trial was designed and powered to provide an effect size estimate that would inform the design and sample size calculations for a future multisite trial. While many pilot studies emphasize feasibility and acceptability as primary outcomes, in this single-site trial, we aimed to generate robust preliminary data on testing uptake to guide scale-up and ensure generalizability across diverse ED settings.

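### The minimum detectable effect of 0.348 behaves as a standardised effect, so restating it as a 35% higher likelihood of testing does not follow without a control testing rate

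*Protocol article*

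**What the plan says.** All the power material is in the Power Analysis section of the protocol article.

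- Sample size: "This pilot trial will enroll 44 providers and 140 adolescent and young adult patients over 6 months based on feasibility".
- Error rates and clustering: "α=.05, a 2-tailed test, with 80% power, and ICC of 0.01".
- Covariates: "50% of variance in adolescents and young adults, and 50% of variance in providers explained".
- Result: "we estimate the minimum detectable effect size (MDE) of 0.348", with no unit or scale attached.
- Restatement of that result for the primary outcome: "we have the power to detect a minimum of 35% higher likelihood of being tested for STIs in the intervention arm", compared with usual care.

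The Primary Outcome section defines the endpoint as "the difference in the proportion of sexually active adolescents and young adults tested" in the two arms. The endpoint is therefore binary and its stated scale is a difference in proportions. The listed power assumptions include no testing rate for the control arm.

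**The concern.** The figure of 35% appears to be 0.348 rounded and renamed. A minimum detectable effect computed from cluster numbers, an ICC and variance-explained terms is a difference in standard deviations. For a binary outcome the standard deviation depends on the testing rate, so the same 0.348 means different absolute and relative changes at different control rates. The article makes the conversion without fixing a rate.

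This is the article's only power statement for the primary outcome. The Primary Outcome section also says the trial was powered to yield an effect estimate for planning a multisite trial. A reader who takes the sentence at face value would credit the pilot with 80% power for an effect that the calculation does not establish.

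**Working it through.** **Inputs.** From Power Analysis: J = 44 providers, N = 140 patients, two-sided alpha 0.05, power 80%, ICC 0.01, R² = 0.50 at each level. From Randomization and Allocation: 1:1 at provider level. Equal arms are assumed (22 providers and 70 patients each), with 140/44 = 3.18 patients per provider.

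**Step 1: reproduce 0.348.** The standard two-level formula for a cluster-randomised standardised effect is

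MDE = (t₀.₉₇₅ + t₀.₈₀) × √[ICC(1 − R²)/(0.25 J) + (1 − ICC)(1 − R²)/(0.25 N)], with J − 2 = 42 degrees of freedom.

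- Multiplier: 2.018 + 0.850 = 2.868.
- Provider term: 0.01 × 0.5 / 11 = 0.000455.
- Patient term: 0.99 × 0.5 / 35 = 0.014143.
- MDE = 2.868 × √0.014597 = 2.868 × 0.12082 = 0.347.

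With 139 patients the result is 0.348. The stated figure is matched to within 0.4%, and power at exactly 0.348 with 140 patients is 80.3%. No testing rate enters the formula, so its output is in SD units.

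**Step 2: put 0.348 SD on the probability scale.** Solve (p₁ − p₀)/√[p̄(1 − p̄)] = 0.348, where p̄ is the mean of the two rates. The article gives no control rate, so p₀ is an assumed range.

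| Control rate | Intervention rate | Difference (points) | Risk ratio |
|---|---|---|---|
| 10% | 22.9% | +12.9 | 2.29 |
| 20% | 35.6% | +15.6 | 1.78 |
| 30% | 46.9% | +16.9 | 1.56 |
| 40% | 57.4% | +17.4 | 1.43 |
| 50% | 67.1% | +17.1 | 1.34 |
| 60% | 76.2% | +16.2 | 1.27 |
| 70% | 84.6% | +14.6 | 1.21 |

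Setting p₁ = 1.35 p₀ in the same equation gives p₀ = 49%. Only there does 0.348 SD equal a 35% relative increase.

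**Step 3: power if 35% means a risk ratio of 1.35.** This uses the two-proportion normal approximation, with variance pooled under the null. The design effect is 1 + (3.18 − 1) × 0.01 = 1.022. To stay consistent with Step 1, the plan's R² of 0.50 is credited by doubling the effective size: 140/1.022 = 137 per arm.

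| Control rate | Power for RR 1.35 |
|---|---|
| 10% | 14% |
| 20% | 28% |
| 30% | 44% |
| 40% | 64% |
| 50% | 84% |
| 60% | 97% |

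Power reaches 80% at a control rate of about 48%. This is slightly below the 49% of Step 2 because the approximation differs. Above that rate power exceeds 80%, so a smaller relative increase is detectable and 35% is not the minimum. The relative reading stops at about 74%, where 1.35 times the rate reaches 100%.

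**Step 4: other readings of 35%.**

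- As 35 percentage points: power is about 99% or more at every control rate checked from 5% to 60%, even without the R² credit. The minimum from Step 2 is about 13 to 17 points.
- As an odds ratio of 1.35: power is 12% to 23% for control rates of 10% to 70% with R² credited. By the logistic conversion, 0.348 SD is an odds ratio of about 1.88.

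**The case against.** **The scale is inferred.** The article never calls 0.348 standardised, and the planned 140 patients give 0.347. This stands as a caveat. It does not rescue the restatement, because the listed assumptions contain no testing rate from which any change in likelihood could be derived.

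**The article may be a condensed account.** A fuller protocol or analysis plan could hold a control rate. That is fair, and the missing rate is not itself the fault. The fault is that the article makes an explicit conversion that its listed assumptions cannot support.

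**The claim is not wrong everywhere.** This stands. At a control rate near 49% the statement is about right, and above about 48% the trial has at least 80% power for a risk ratio of 1.35. A reader might infer that the trial is underpowered for a 35% relative increase at most plausible control rates. The documents do not support that, because they give no control rate and do not say which rates are plausible. The figure of under 5% in the Introduction concerns screening of patients with symptoms suggesting extragenital infection, which is a different quantity.

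**Lower power figures can be produced.** Dropping the R² credit gives 16%, 25%, 37% and 55% at control rates of 20%, 30%, 40% and 50%. Those are not like for like, since the credit is needed to obtain 0.348. They combine the scale error with a separate question about the variance-explained assumption.

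**Little depends on it.** The sample size rests on feasibility, enrolment is complete, and the multisite trial is to be sized from the observed effect. This stands, and it limits the consequence to how the pilot's sensitivity is reported. A reader might also infer that a null result would be taken to exclude a 35% increase, but no section plans that interpretation.

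**Conclusion.** The restatement is invalid and should be corrected. The value 0.348 fits the stated inputs as a standardised effect, and it corresponds to about 13 to 17 percentage points over control rates of 10% to 70%.

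The direction of the error depends on what 35% is taken to mean. As a relative increase, power is overstated below a control rate of about 48% (for example 44% at a 30% rate), and above it 35% is not the minimum. As percentage points, the sentence understates what the trial can detect by a factor of about two. It therefore cannot be said in general that the correct figure is less favourable.

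These results assume equal arms, the two-level formula and the plan's 50% variance explained at each level. The control rates are an assumed range.

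**What to change.** In Power Analysis, delete the 35% statement and say that 0.348 is a standardised effect in SD units. Then give the minimum detectable difference in percentage points, which is the scale of the primary outcome. State it at a named control testing rate taken from pre-trial information, such as the EDs' own earlier records, or as a short table across a range of rates like the one in Step 2. If a risk ratio is also wanted, report it beside the control rate to which it belongs. The rate should not come from the trial's own results.

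The cost is one sentence and a small table. Enrolment and the analysis model do not change. Since analyses were still underway when the article was written, the correction can be made in reporting the results.

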### Ethical Considerations

This study was reviewed and approved by the Institutional Review Board (IRB) at Columbia University (Protocol #AAAU7485). Written informed consent was obtained from all adult participants. For participants aged between 14 and 17 years, a waiver of parental consent was granted by the IRB, and assent was obtained using a standardized script and study summary tailored for adolescent comprehension. Agreement to participate was confirmed verbally in the presence of 2 study staff (typically the research coordinator and the physician attending the ED) to ensure understanding and voluntariness. All data are deidentified for analysis to ensure participant confidentiality. Participants received a US $10 pay card as compensation for their time.

## Results

Enrollment began in September 2023 and was completed in July 2025, with 44 providers and 139 adolescent and young adult participants enrolled across adult and pediatric EDs. All participants’ follow-up and survey data collection are complete. Data cleaning and primary analyses are currently underway, with dissemination of final results anticipated in late 2025.

## Discussion

### Hypothesis

This protocol outlines an RCT to assess the preliminary efficacy and implementation of the STIckER app, a shared decision-making tool to support gonorrhea and chlamydia testing in adolescents and young adults in EDs. We anticipate that the intervention will lead to a higher proportion of adolescents and young adults receiving comprehensive genitourinary and extragenital STI testing compared to usual care, and that both patients and providers will find the tool acceptable, appropriate, and feasible to implement.

### Comparison With Previous Work

Previous studies have highlighted significant gaps in STI testing, particularly for extragenital sites, in both outpatient and ED settings [3,29,30]. While SDM tools have been shown to improve patient engagement and outcomes in other areas of emergency medicine, such as analgesic choice and evaluation of chest pain, few, if any, have focused on sexual health. STIckER addresses this gap by applying the SDM model to STI testing decisions in the ED [15-19,31], a critical access point for many underserved youths [5,32]. By centering the patient’s values and preferences, this tool has the potential to both improve care and reduce disparities in STI screening access.

Beyond sexual health, a broader body of work on mHealth in emergency settings demonstrates the feasibility and moderate effectiveness of digital interventions across diverse health domains. For example, randomized trials of text-message interventions have shown reductions in hazardous drinking among young adults [33], while culturally tailored apps and SMS programs improved blood pressure control among Black adults with hypertension [34] and increased asthma-related follow-up visits for children [35]. Interventions that were linguistically accessible and rooted in behavioral change theory were most successful, underscoring the potential of ED-based digital tools like STIckER to promote equitable, patient-centered screening.

